### Randomization

Randomization to either *myCompass* or the active placebo intervention will be carried out after baseline measurement, according to a sequence generated by a computerized random-number generator [32] using permutated blocks of 2, 4, and 8. The randomization process will be facilitated by a researcher not involved with the study. Participants will receive login details for their respective interventions by email.

### Measures

The assessments that will be completed at baseline, post-treatment, and 3-months follow-up are summarized in Table 1. Demographic data will include gender, age, marital status, highest education level, and whether the young person is currently working and/or studying. Disease-related information will include age at diagnosis, treatment modality, and diabetes complications status. Participants will also nominate their general practitioner (GP) and diabetes specialist in order to facilitate risk management and the collection of HbA1c results by research personnel.

**Table 1 table1:** Measures used at screening, baseline, post intervention, and 3- month follow-up.

Measure	Screening	Baseline	Post-test	3 months
Demographic and disease-related variables		X^a^		
Psychosis Screening Questionnaire (PSQ)	X			
Patient Health Questionnaire-9 (PHQ-9)	X		X	X
Generalized Anxiety Disorder-7 (GAD-7)		X	X	X
Diabetes Distress Scale (DDS)	X		X	X
Warwick-Edinburgh Mental Well-being Scale (WEMWBS)		X	X	X
Work and Social Adjustment Scale (WSAS)		X	X	X
Summary of Diabetes Self-Care Activities (SDSCAS)		X	X	X
Hyperglycemia/Hypoglycemia scale		X	X	X
Glycosylated haemoglobin (HbA1c)		X	X	X
Mental Health Self-Efficacy Scale (MHSES)		X	X	X

^a^The X indicates the time-points at which the specific measure will be administered.

### Primary Outcome Measures

#### Depression Symptoms

The Patient Health Questionnaire-9 (PHQ-9) [29] contains 9 items assessing the Diagnostic and Statistical Manual of Mental Disorders (DSM)-IV criteria for major depressive disorder (MDD). The scale has excellent psychometric properties [33], and identifies similar rates of MDD when compared to semi-structured clinical interviews of DSM criteria in both adults [34] and adolescents [35]. It is used widely as a screening tool for depression, and is frequently included as outcome measures in studies of online interventions (eg, [36,37]). Scores of 5, 10, 15, and 20 are used as cut-off points for mild, moderate, moderately severe, and severe depressive symptoms, respectively.

#### Anxiety Symptoms

The Generalized Anxiety Disorder-7 Questionnaire (GAD-7) [38] contains 7 items assessing DSM-IV criteria for generalized anxiety disorder (GAD). The scale is well-validated as a screener for GAD [33], used frequently in an online format (eg, [36,37]), and shows good sensitivity and specificity for anxiety disorders generally [39]. Scores of 5, 10, and 15 represent cut-off points for mild, moderate, and severe anxiety symptoms, respectively.

#### Diabetes-Related Distress

The Diabetes Distress Scale (DDS) [28] is a 17-item scale that assesses the following four areas of diabetes-related emotional distress (1) emotional burden, (2) physician-related distress, (3) regimen-related distress, and (4) diabetes-related interpersonal distress. Scores on the DDS are calculated as the mean of all items and range from 1-6, with scores of >2 indicating “*little or no distress*”, and ≥3 indicating “*high distress*”. Data support the psychometric adequacy of the DDS when used in adult and adolescent samples [28,40].

#### Well-being

The Warwick-Edinburgh Mental Well-being Scale (WEMWBS) [41] is a 14-item scale that measures mental well-being through the concepts of positive affect, psychological functioning, and interpersonal relationships, and is validated for measuring mental well-being in young people aged ≥16 years [42]. Scores range from 14-70, with higher scores indicating more positive mental well-being.

### Secondary Outcome Measures

#### Work and Social Adjustment

The 5-item Work and Social Adjustment Scale (WSAS) [43] is a measure of the impact of mental health problems on daily functioning in the following five domains (1) work, (2) social leisure activities, (3) private leisure activities, (4) home management, and (5) personal relationships. Scores range from 0-40, with higher scores indicating poorer adjustment. Meyer et al [44] provide data supporting the psychometric adequacy of the WSAS when used in an online format.

#### Diabetes Self-Care

The 11-item Summary of Diabetes Self-Care Activities Scale (SDSCAS) [45] will be used to measure diabetes self-management. Participants rate how many days out of the past seven they have engaged in such activities as healthy eating, exercise, testing blood sugar, and foot care. Mean scores are calculated for each area and range between 0-7, with higher scores representing better self-care. Reviews support the reliability and validity of the SDSCAS as a self-report measure of diabetes self-management [45].

#### Glycemic Control

The 7-item Hyperglycemia Scale and 7-item Hypoglycemia Scale [46] will be used to assess participants’ self-reports of symptoms associated with high and low blood glucose, respectively. Additionally, as an objective indictor of glycemic control, participants’ HbA1c results will be retrieved from medical records (see Figure 1). The measurement of HbA1c provides an index of glycemic control over the preceding 2-3 months, and is useful for evaluating whether a person has achieved and maintained their treatment targets, as well as estimating their risk of chronic diabetes complications [47].

### Process Measures

#### Mental Health Self-Efficacy

The Mental Health Self-Efficacy Scale (MHSES) assesses people’s confidence in managing issues relating to their mental health using six, 10-point Likert scale items. Item scores are summed to obtain an overall measure (ranging from 6-60), with higher scores indicating greater mental health self-efficacy. The MHSES yields reliable and valid data, and is sensitive to change [48].

#### Program Usage

Usage will be examined for the *myCompass* group with respect to three indices, namely, frequency of logins, frequency of self-monitoring, and number of modules attempted.

### Risk Management Protocol

If any participant indicates a significant worsening of their psychological distress (defined as a score of >19 on the PHQ-9 either midway through the intervention period, at post-intervention, or follow-up) they will be sent an email from the research team advising them to contact their GP to arrange face-to-face support. A second email, sent 3 days later, will seek confirmation that contact with the GP has been made. If no contact has been made, or if no reply email is received, participants will be informed by email that the principal investigator of the study will contact their nominated GP to recommend they receive appropriate face-to-face support.

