## Methods

### Study Design

A 2 (conditions) x 3 (time) RCT design is planned. Participants will be randomized to either the *myCompass* intervention or an active placebo intervention, and each group will have full program access for 7 weeks. Outcomes will be assessed at baseline, post-intervention (8 weeks), and three months follow-up (Figure 1).

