#### Active Placebo

The comparator intervention will be an Internet-delivered program called *LiveWell* which delivers health information about a range of topics including skin care, mobile phone use, home environment, casual work, healthy food, and relationships. Developed by the research team to match *myCompass* on duration and mode of delivery, the program also contains practice activities, home tasks, and factual SMS messages (sent to participants once-weekly), and a symptom check at 4 weeks, to replicate the interactivity of *myCompass*, but has no therapeutic content.

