## Results

### Sample Size

The RCT of *myCompass* yielded an average between-group effect size on symptom outcomes of d=0.5 [25]. Van Bastellar et al [22] also reported controlled effect sizes of an online intervention for people with diabetes in the vicinity of d=0.5 for diabetes-related distress and depressive symptoms. Assuming an attrition rate of 50% [49,50], a total sample of 240 participants at follow-up (120 per arm) is the minimum required to detect between-group differences on self-report outcomes of .5 standard deviations with 80% power.

Nevertheless, we will aim for a final sample size 280 participants (140 per arm), as we have pilot data showing that this will enable us to detect a clinically meaningful decrease in HbA1c of 0.5% with power at 80%. This is based on analysis of clinic patients at Sydney Children’s Hospital, revealing a standard deviation of 1.04 for the change in HbA1c over 3 months. Recruitment is currently underway for this study.

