### Statistical Analysis

Analyses will be completed with SPSS 22 software. Chi-squares (categorical variables) and *t* tests (continuous variables) will be used to compare demographic and disease-related variables and baseline scores on the outcome measures for the intervention and attention control groups. Similar analyses will be performed comparing participants who do (non-dropouts) and do not (dropouts) return completed questionnaires at each of the post-intervention and follow-up assessments to explore possible biases in study attrition.

Outcomes at each time point will be analyzed on an intention-to-treat basis using linear mixed modeling (LMM) [51], with time points as a within-group factor and intervention as a between-group factor. In LMM, incomplete cases are included in the analysis, and all available data is used to obtain parameter estimates. The interaction of time and study condition will be of primary interest in each analysis, with a significant interaction indicating a group difference in the pattern of change over time in the outcome of interest. Significant interactions will be explored using sets of Bonferroni adjusted comparisons of the two groups at post-intervention and 3-month follow-up. All effects will be tested at *P*<.05, with adjustment according to the number of contrasts in each set. Within- and between-group effect sizes will be calculated using Cohen’s d (based on the pooled standard deviation).

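### The risk rule implies a midway PHQ-9, but Table 1 and the three-time-point design leave it out; adding it to the PHQ-9 model is a cheap improvement

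*Protocol article*

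**What the plan says.** All references are to the protocol article.

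- **Risk Management Protocol.** The rule opens with "If any participant indicates a significant worsening of their psychological distress", which is "defined as a score of >19 on the PHQ-9 either midway through the intervention period, at post-intervention, or follow-up". It is not restricted by arm and cannot operate midway without a midway PHQ-9.
- **Active Placebo.** The control program contains "a symptom check at 4 weeks, to replicate the interactivity of" *myCompass*. The instrument is not named.
- **Study Design.** "A 2 (conditions) x 3 (time) RCT design is planned", and "Outcomes will be assessed at baseline, post-intervention (8 weeks), and three months follow-up".
- **Measures, Table 1.** The caption reads "Measures used at screening, baseline, post intervention, and 3- month follow-up". The PHQ-9 is marked at screening, post-test and 3 months, and there is no midway column.
- **Statistical Analysis.** A linear mixed model is planned, in which "incomplete cases are included in the analysis, and all available data is used to obtain parameter estimates". Group comparisons are at post-intervention and 3 months. The section neither includes nor excludes a midway score.
- **Sample Size.** The calculation begins "Assuming an attrition rate of 50" per cent, and the target is 280 participants.

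**The concern.** The PHQ-9 is a primary outcome. By Table 1, a midway score would be the only PHQ-9 taken between screening and week 8. The safety section relies on it, while the schedule and the three-level time factor omit it.

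A likelihood-based mixed model is valid when dropout depends only on scores that are in the model. For a participant who leaves after the midway check and does not return, a model without that score predicts the missing values from a pre-treatment score alone. Two things are at stake:

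- **Precision**, which is lost whenever some week-8 dropouts have a midway score.
- **Plausibility of the missing-at-random assumption**, which is weaker if response during treatment influences who stays, particularly if it does so differently in the two arms.

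**Working it through.** **1. Plan's own figure.** The plan gives no figure for this point; only the attrition rate bears on it. Reading 280 as the number enrolled, 280 × 0.50 = 140 people would lack follow-up data. Only those who reached and completed the midway check could supply a midway score.

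**2. Assumptions.** The documents give no correlations and no midway completion rate. Correlations are written as r_b (baseline-week 8), r_m (midway-week 8) and r_bm (baseline-midway). All scores have unit SD. The fraction observed at week 8 is f = 0.5, and the fraction with a midway score is g ≥ f. Loss is monotone, baseline means are common to the arms, and there is no 3-month score.

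**3. Precision formula.** With N per arm:

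- Without midway: V0 = (2/N) × (1 − r_b²)/f
- With midway: V1 = (2/N) × [(1 − r_b²)/f − q(1/f − 1/g)], where q = (r_m − r_b·r_bm)²/(1 − r_bm²)

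The gain in precision is V0/V1 − 1, and N cancels.

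Worked example with r_b = 0.5, r_m = 0.7, r_bm = 0.6 and g = 0.75: q = (0.7 − 0.30)²/0.64 = 0.25. Then (1 − 0.25)/0.5 = 1.5, and 1.5 − 0.25 × (2 − 1.333) = 1.333. The ratio is 1.5/1.333 = 1.125, a gain of 12.5%.

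| r_b, r_m, r_bm | q | g = 0.50 | g = 0.60 | g = 0.75 | g = 1.00 |
|---|---|---|---|---|---|
| 0.5, 0.6, 0.6 | 0.141 | 0% | 3.2% | 6.7% | 10.3% |
| 0.5, 0.7, 0.6 | 0.250 | 0% | 5.9% | 12.5% | 20.0% |
| 0.4, 0.8, 0.5 | 0.480 | 0% | 10.5% | 23.5% | 40.0% |

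The column g = 0.50 is the case where no week-8 dropout completed the midway check.

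**4. Power.** With N = 140, g = 0.75, a difference of 0.5 SD and a single two-sided 5% contrast, the standard error in the middle row falls from √(2/140 × 1.5) = 0.146 to √(2/140 × 1.333) = 0.138. Power goes from 93% to 95%. Over the three rows it goes from about 90-93% to 94-95%.

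**5. Sensitivity.**

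- If 65% are observed at week 8 and g = 0.75, the middle row gives 1.154/(1.154 − 0.25 × 0.205) = 1.047, a gain of about 5%.
- If baseline means differ by arm and the contrast is change from baseline, (1 − r_b)² is added to both brackets. The middle row at g = 0.75 becomes 1.75/1.583 = 1.105, a gain of about 11%.

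**6. Bias.** A large-sample simulation used the middle-row correlations, with true differences of −0.30 midway and −0.50 at week 8. Week-8 dropout was 50% and logistic in the midway score (log-odds 1 per SD where it depends). Every dropout had a midway score.

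| Dropout mechanism | Estimate without midway | Estimate with midway |
|---|---|---|
| Random | −0.50 | −0.50 |
| Same in both arms | −0.50 | −0.50 |
| Control arm only | −0.33 | −0.50 |
| *myCompass* arm only | −0.67 | −0.50 |
| Opposite directions | −0.15 | −0.51 |

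The last three rows are best cases for the point. With baseline-midway correlation 0.55, log-odds 0.5 to 1.0, and most losses occurring at random before midway (25 of 35 percentage points, or 40 of 50), the control-only estimate without midway is about −0.43 to −0.47.

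**The case against.** - **Collection is inferred.** The risk rule is a conditional trigger, not a schedule. The 4-week check names no instrument, and the *myCompass* section describes no such check. This stands: collection from every participant is not established. A midway PHQ-9 is still implied in both arms, because the rule covers any participant.
- **Exclusion is inferred.** A reader might conclude that the plan discards the score. Statistical Analysis does not say so; the omission follows from the 2 × 3 design and Table 1. The unseen analysis plan may cover it.
- **Omission is not an error.** A reader might conclude that the planned model is biased. The documents do not support that. A mixed model on the scheduled assessments is standard, and material bias here needs dropout that depends on the midway score differently by arm, for which the text gives no evidence.
- **The size is conditional.** The 50% attrition is tied to follow-up, and no week-8 rate is given. A week-8 non-responder may return at 3 months, and that score then informs week 8. People who leave before midway gain nothing. All of this stands and lowers the expected benefit.
- **A fourth occasion changes the primary test.** The default interaction goes from (3 − 1)(2 − 1) = 2 to (4 − 1)(2 − 1) = 3 degrees of freedom and takes in the week-4 difference. This stands, and the fix has to deal with it.

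**Conclusion.** The point holds as an inconsistency to reconcile and an inexpensive improvement, not as a fault in the model. The risk rule uses a PHQ-9 occasion that Study Design and Table 1 do not contain.

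On the stated assumptions, including that score raises the precision of the week-8 PHQ-9 difference by about 3-11% at 60% midway completion and 7-24% at 75%. The gain is nil if no week-8 dropout completed it, and smaller than these figures if less than 50% is missing at week 8 or if dropouts return at 3 months.

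Including the score also protects against dropout that depends on midway response differently by arm. The size of that protection cannot be settled from the documents, and the simulated values only illustrate it.

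**What to change.** 1. Reconcile Risk Management Protocol, Active Placebo, Study Design and Table 1. State whether the midway PHQ-9 is taken in both arms and, if it is as the risk rule implies, list it in Table 1. The risk rule itself need not change for this purpose.
2. Include the midway PHQ-9 in the PHQ-9 mixed model as an additional post-randomization occasion with unstructured covariance.
3. Keep the week-4 difference out of the primary test. With d(t) as the group difference at time t, test jointly d(week 8) − d(baseline) = 0 and d(3 months) − d(baseline) = 0, on 2 degrees of freedom, leaving d(week 4) free. Make follow-up comparisons only at week 8 and 3 months, with the planned Bonferroni adjustment.
4. Fix this before outcome data are seen by arm; recruitment is already under way.

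**Cost.** A few more covariance parameters, a custom contrast in place of the default interaction test, and export of the midway score. If the score is already taken for safety, no visit, questionnaire or participant is added.

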#### Eligibility

Young people will be eligible for the trial if they are an Australian resident aged between 16-25 years (inclusive), have an email address and Internet access (via mobile phone, and computer or tablet), were diagnosed with type 1 diabetes by a specialist clinician, and have at least mild symptoms of psychological distress. In light of research suggesting that mental health problems (especially those in the subclinical range) in people with diabetes may, in part, reflect disease-specific distress [26], and given calls for routine screening of both general and diabetes-specific distress in diabetes patients [27], a young person will meet our inclusion criteria if they have a mean score of ≥2 on the Diabetes Distress Scale (DDS) [28], and/or a total score of ≥5 on the on the Patient Health Questionnaire (PHQ) [29]. Exclusion criteria include the inability to read English easily, previous use of the *myCompass* intervention, and current psychotic symptoms (total score of ≥2 on the Psychosis Screening Questionnaire (PSQ) [30] (Textbox 1). Screening will be automatically stopped and appropriate feedback provided if any responses indicate ineligibility.

Inclusion and exclusion criteria.CriteriaInclusionConsent to participateAge 16-25 yearsType 1 diabetes, diagnosed by an endocrinologistAccess to an Internet-enabled mobile phone and computer/tabletPatient Health Questionnaire (PHQ-9) score of ≥5 and/or Diabetes Distress Scale score of ≥2ExclusionInability to read English with easePrevious experience with the *myCompass* programPsychotic symptomsNon-residence in Australia

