### Intervention and Control

#### myCompass

The *myCompass* program [31] is a fully-automated public health intervention with no therapist input that can be accessed via any Internet-enabled mobile phone, tablet, or computer (Figure 2). Developed by mental health researchers at the Black Dog Institute, the program assesses users’ self-reported mental health symptoms on registration, and delivers a personalized intervention that provides round-the-clock self-monitoring of moods and behaviors (via mobile phone, tablet, or computer), and access to twelve interactive evidence-based learning modules (via tablet and computer). The modules provide skills training drawn from cognitive behavioral, interpersonal, problem solving, and positive psychology therapies, and cover such topics as solving problems, managing fear and anxiety, tackling unhelpful thinking, dealing with stress and overload, and increasing pleasurable activities. Each module comprises three 10-minute sessions and has practice activities and home-tasks assigned. Users are encouraged to complete at least two modules, either of their own choosing or from recommendations provided on registration.

In addition, users can schedule short message service (SMS) or email reminders to facilitate self-monitoring. Reminders can be used to receive and print graphical feedback about self-monitoring (including contextual information) on mobile phones or computers to monitor change and assist identification of triggers. It is also possible to receive helpful facts, mental health-care tips, or motivational statements by SMS or email. Registering to use the program is free, and users are not billed for the SMSs they receive. A detailed description of the *myCompass* intervention is provided in [name] et al [25].

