### Procedure

Participants will have access to the full intervention on their mobile phones and computer devices for 7 weeks. Although participants will be encouraged to use the programs ad libitum during the intervention period, it will be recommended that they complete at least two program modules in their own time. Assessment will be conducted completely online. At each assessment time-point, participants will receive an email asking them to log into the study website to complete the outcome measures. The email sent at 3-months follow-up will also prompt participants to visit their diabetes specialist for assessment of glycosylated haemoglobin (HbA1c).

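### The GP-advice rule for PHQ-9 above 19 leaves out screening, so an eligible person already in the severe band is randomized with no advice under that rule

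*Protocol article*

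**What the plan says.** The Risk Management Protocol section of the article gives a complete rule. The trigger is "defined as a score of >19 on the PHQ-9 either midway through the intervention period, at post-intervention, or follow-up". The participant is then emailed advice to see their GP. A second email 3 days later asks whether this has happened. If it has not, or if no reply comes, the principal investigator contacts the GP.

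Other sections fix what happens before the first of those times:

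- **Eligibility.** A PHQ-9 total of 5 or more, and/or a mean Diabetes Distress Scale score of 2 or more, qualifies. No upper PHQ-9 limit is given, and no exclusion covers severe depression. On feedback the section says: "Screening will be automatically stopped and appropriate feedback provided if any responses indicate ineligibility".
- **Measures, Table 1.** The PHQ-9 is marked at screening, post-test and 3 months. The text adds: "Participants will also nominate their general practitioner (GP) and diabetes specialist in order to facilitate risk management".
- **Depression Symptoms.** A score of 20 is the cut-off for severe symptoms.
- **Randomization.** Allocation "will be carried out after baseline measurement".
- **Intervention and Control.** myCompass is a "fully-automated public health intervention with no therapist input". The LiveWell comparator imitates its interactivity "but has no therapeutic content".

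**The concern.** The plan treats a PHQ-9 above 19 as a reason to seek face-to-face support from a GP. It holds such a score for some people before they are randomized, yet the stated rule does not act on it then. Those people may be allocated to an automated program without a therapist or to a placebo program. The same score obtained some weeks later would start the emails and the GP contact.

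This is a matter of participant safety. The age range is 16 to 25, the trial runs entirely online, and the Sample Size section says recruitment has begun. Estimates, error rates and power are not at issue.

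**Working it through.** The plan gives no figure to reproduce here, so the check sets the sections side by side.

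**1. Can a severe scorer enter?** Yes. A score of 20 or more meets the PHQ-9 criterion on its own. The listed exclusions (English reading, previous myCompass use, psychotic symptoms, living outside Australia) do not remove such a person.

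**2. Does screening give them advice?** Not as stated. Feedback is tied to responses that show ineligibility, and a high PHQ-9 is not one of them.

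**3. Is the score known before allocation?** Yes. Screening comes before baseline, and randomization follows baseline. Table 1 marks no separate baseline PHQ-9, so the screening score is the only one before randomization. It is also the only PHQ-9 that every randomized participant has completed.

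**4. When can the rule first act?** Midway. Half of the 7-week program is 7 / 2 = 3.5 weeks. The Active Placebo section mentions a symptom check at 4 weeks, without naming the PHQ-9, and Table 1 has no midway column. The interval from screening to randomization is not stated. The documents therefore support *about mid-program* and nothing more exact.

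**5. Is it certain to act then?** No, for two reasons.

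- It needs a returned questionnaire. The Procedure section says: "At each assessment time-point, participants will receive an email asking them to log into the study website". The Sample Size section assumes 50% attrition.
- It needs a score still above 19. Someone at 20 or more at screening and 19 or below later never triggers it.

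**6. Is the trigger one that could apply at screening?** Yes. The section calls it a worsening, but the definition compares with nothing. Someone who goes from 22 to 20 has improved and triggers it; someone who goes from 5 to 19 has worsened and does not. A rule based on level can be applied at entry as readily as later.

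**7. How many people?** The documents give no PHQ-9 mean or standard deviation (SD) for this population. As an illustration only, assume normal scores rounded to whole numbers, so that above 19 means at least 19.5, and take 280 participants.

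- Low case, mean 8 and SD 4: z = (19.5 − 8) / 4 = 2.875, upper tail 0.0020, and 0.0020 × 280 = 0.6.
- High case, mean 12 and SD 6, with everyone entering at PHQ-9 of 5 or more: z = (19.5 − 12) / 6 = 1.25, upper tail 0.1056. The share at 5 or more is the probability above 4.5, which is 0.8944. Then 0.1056 / 0.8944 = 0.118, and 0.118 × 280 = 33.

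A range of about 1 to 33 only reflects the assumptions. It shows that the number cannot be stated from the documents.

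**The case against.** The strongest reply is that this is a condensed article. The section concerns the monitoring of enrolled participants, and handling at entry may sit in the full protocol, the screening website or the participant information, none of which is shown. Ethics and site governance approval are on record. This stands in part: nobody can say from the article that the trial has no such step. It does not remove the point, because the article does more than stay silent. It sets out the threshold, the times, the emails, the interval and the escalation, and the times leave out entry.

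A second reply is that the rule addresses worsening, which screening cannot show. That fits the label but not the definition, which is a level.

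A third concerns context. Participants are invited by clinical staff during routine visits to hospital diabetes services, and myCompass assesses symptoms on registration and personalizes its content from them. A reader might infer from the gap that severe entrants have no care at all, and the documents do not support that. Equally, no section passes the screening score to the clinic or the GP, and personalizing a self-help program is not a stated safety response.

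Two further inferences should be resisted:

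- **That a known share of severe entrants is missed at midway.** Any such percentage rests on an assumed correlation, mean change and non-response. It also counts people who have left the severe band together with people who are overlooked.
- **That half of 280, or 140, would return nothing.** The Sample Size section speaks of 240 at follow-up and a final sample of 280, while the Abstract speaks of recruiting 280. Whether 280 is before or after attrition is unclear, and when people drop out is not stated.

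**Conclusion.** The point holds in a limited form. Under the rule as written, an eligible person with a screening PHQ-9 of 20 or more is randomized with no GP advice until about mid-program. They receive none if they return no later questionnaire or never again score above 19. The article states no other step for them.

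This follows from the text alone and needs no assumption about the distribution of scores. It is confined to the stated rule, since the full protocol cannot be seen, and the number affected is unknown. The threshold of 19 is sound as a safety trigger. Renaming the rule so that it no longer speaks of worsening would be tidier but would change nothing for participants. No outcome analysis is affected.

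**What to change.** Add screening to the listed times. A screening PHQ-9 above 19 would then start the same first email, 3-day check and GP contact, once the GP is nominated at baseline and before randomization, identically for all participants. If the full protocol already has such a step, naming it in this rule settles the point.

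For anyone already randomized with a screening score above 19, make the same contact in both arms without regard to allocation, and record it. This contact comes after allocation, so the reassurance about bias given below for new entrants does not carry over to it automatically.

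The cost is small: one sentence in the risk protocol, an ethics amendment because recruitment is under way, and a few extra emails. The score and the GP's details are already collected. The downside is that a few participants may start GP care alongside their program. For new entrants the step begins before allocation and is the same in both arms, so it does not bias the comparison, although it could slightly reduce the between-group difference.
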